2.4.4 Trial flow Chart

The trial flow chart and the schedule of enrollment, interventions, and assessments are shown in Supplementary Figure S3 and Table S1.

[figure not shown]

**Supplementary Figure S3. Trial flow chart**

**Table S1. Time of visit and data collection**

|  | **Baseline** | **Allocation** | **Treatment** | | | | | **Follow-up** | |
| --- | --- | --- | --- | --- | --- | --- | --- | --- | --- |
| Time point (Week) | -1 | 0 | 1 | 2 | | 3 | 4 | 8 |  |
| **Enrollment** |  | | | |  |  |  |  |  |
| Signing consent | **×** |  |  |  | |  |  |  |  |
| Screening | **×** |  |  |  | |  |  |  |  |
| Dose of levodopa | **×** |  |  |  | |  |  |  |  |
| Randomization |  | **×** |  |  | |  |  |  |  |
| **Interventions** |  | | | |  |  |  |  |  |
| Manual acupuncture group |  |  | **×** | **×** | | **×** | **×** |  |  |
| Sham acupuncture group |  |  | **×** | **×** | | **×** | **×** |  |  |
| **Assessments** |  | | | |  |  |  |  |  |
| Weekly CSBMs | **×** | **×** | **×** | **×** | | **×** | **×** | **×** |  |
| CSEAS |  | **×** |  |  | |  | **×** | **×** |  |
| PAC-QOL |  | **×** |  |  | |  | **×** | **×** |  |
| UPDRS |  | **×** |  |  | |  | **×** | **×** |  |
| Assessment of blinding |  | **×** |  |  | |  |  | **×** |  |
| Adverse events |  |  | **×** | **×** | | **×** | **×** |  |  |

Weekly CSBMs= weekly complete spontaneous bowel movements; CSEAS=Constipation Symptom and Efficacy Assessment Scale; PAC-QOL= Patient-Assessment of Constipation Quality of Life questionnaire; UPDRS= Unified Parkinson’s Disease Rating Scale.

2.4.5 Outcomes Measurements

2.4.5.1 Primary Outcome

**2.4.5.1.1** **The change of weekly complete spontaneous bowel movements (CSBMs).**

We use weekly CSBMs to observe changes in the number of bowel movements in patients with constipation. CSBMs are defined as the number of bowel movements that have occurred in the past 24 hours without the use of emergency medication. CSBMs are recorded by patients on an electronic bowel diary under the direction of an independent outcome assessor. Weekly CSBMs will be collected at baseline (week 0), post-treatment (week 4), and follow-up (week 8), and differences from baseline levels are compared at weeks 4 and 8.

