2.4.1.3 Blinding

This study will be blinded to patients, outcome assessors, and statisticians. The treatment time for patients in different groups will be set at different times of the day to prevent communication between the two groups. During the treatment, the patients will be required to wear an eye mask to ensure the implementation of the blinding method. All operations will be performed according to a standardized procedure to ensure consistency of operation. The efficacy assessor will not be involved in the grouping and treatment manipulation. The blinding will be removed at the end of the treatment, and patients will be informed of their grouping after treatment as well as will be told their type of acupuncture after follow-up.

This study will be controlled using a special acupuncture device which was developed and designed by our team members. The special acupuncture device was shown in Supplementary Figure S2. The acupuncture device consisted of a base, a cannula, and a specially designed acupuncture needle. There are classified into two types of bases. In the MA group, the base has a longitudinal opening at the bottom, through which acupuncture needles can be pierced into the skin. Conversely, the SA group's base has a closed adhesive with no opening at the bottom, so special flat-head needling can contact the skin through the adhesive but cannot pierce it. The cannula is removable and can be adjusted to meet the needs of various needling angles depending on the site of needling. The special flat-head needle has the same shank as ordinary acupuncture needle. Since the flat-head needle do not actually pierce the skin, it is designed to be shorter in length than ordinary acupuncture needle, and the length of the body exposed during needling is the same as that of ordinary acupuncture needle to ensure consistency of appearance during operation.

The special acupuncture device to be used in this study has been approved for a national utility model patent, with the patent number ZL202121352221.7 and is produced by a manufacturer with relevant qualifications (Guangzhou Suixin Medical Equipment Co., Ltd.). The related article has been published(Wang et al., 2022).

[figure not shown]

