2.4.3 Subjects

2.4.3.1 Inclusion criteria

(1) Meeting the Movement Disorder Society's revised clinical diagnostic criteria for Parkinson's disease in 2015.

(2) Meeting the diagnostic criteria for functional constipation in the Rome IV diagnostic Criteria.

(3) Between 35 and 80 years of age.

(4) Those with Hoehn-Yahr grade of Parkinson's disease ≤ 3.

(5) No medications taken within 2 weeks prior to treatment that may affect gastrointestinal function, such as prucalopride and probiotics.

(6) No participation in other clinical trials such as drugs or acupuncture within 1 month prior to inclusion in this study.

(7) Voluntary engagement in this study and ability to sign the informed consent.

(8) Good compliance, ability to understand the study content, and cooperation in the completion of the bowel symptom diary and scale filling.

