2.4.3.3 Shedding and rejection criteria

A case is considered to be shed if any of the following criteria are met.

(1) Refusal to cooperate with the study arrangements for personal reasons and no longer suitable to continue the study after assessment.

(2) Sudden onset of serious illness, who is assessed to be unfit to continue with the study.

(3) The occurrence of a serious adverse event or an unexpected event.

(4) Those who withdraw from the study on their own.

A case is considered to be rejected if the following conditions are met.

(1) Those who have not completed treatment as required by this study, or the dose or dosing regimen of the anti-Parkinsonian drug need to be adjusted during treatment.

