4.1 Basic treatment of Parkinson's disease

Both groups will be given basic treatment for PD. Throughout the study, patients in both the MA and SA groups will be required to maintain effective therapeutic doses of anti-Parkinson's drugs at levels like their baseline. Patients with any dosage adjustment, whether an increase, decrease, or adjustment, will be dropped.

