4.4 Emergency treatment

When patients don`t have bowel movements for more than three consecutive days or experience intolerable symptoms such as bloating due to constipation, they are allowed to use emergency medications under medical supervision with detailed documentation. The emergency treatment consisted of lactulose and glycerin enemas. Lactulose will be used for patients who do not have bowel movements, and glycerin enemas will be used for patients who strain during defecation. The specifications of the emergency medications are as follows: Lactulose Oral Liquid (Hunan Keren Pharmaceutical Company, Approval No.: State Pharmaceutical Code H20093523), 15 ml per dose at 12-hour intervals, 2 doses in total; Glycerin Enemas (Guangdong Hengjian Pharmaceutical Company, Approval No.: H44023815), 1 stick each time in total.

5. Statistical analysis and processing

SPSS 26.0 will be used as the statistical analysis software for this study. We used the intention-to-treat (ITT) principle, regardless of whether the patients completed all assigned intervention sessions. Continuous variables were expressed as mean (SD) or median (IQR); independent t-tests were used for normally distributed values, and Mann-Whitney U tests were used for skewed data. Categorical variables were expressed as frequencies and percentages and analyzed using the χ2 or Fisher exact test, as appropriate. A repeated measures analysis of variance (ANOVA) was used to detect trends in score changes and treatment effects at different time points within groups. Multiple interpolation (MI) methods were used to estimate missing data for the primary and secondary outcomes. To assess the robustness of MI methods under the assumption of randomization, sensitivity analyses of the primary outcome were performed using per-protocol (PP) sets. Differences between groups were reported using 95% confidence intervals and bilateral P values, with values less than 0.05 considered significant.

Safety analysis: Adverse events are analyzed in all participants who received treatment, including the incidence of adverse events and the specific description of adverse events. The data are summarized as n (%). χ2 test or Fisher’s exact test is used for the comparison between treatment groups.

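### The written definition of the primary outcome does not match its name: it omits completeness and disqualifies a movement only after the two listed emergency drugs.

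*Protocol*

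**What the plan says.** The definition in Protocol section 2.4.5.1.1 reads: "CSBMs are defined as the number of bowel movements that have occurred in the past 24 hours without the use of emergency medication". Patients enter the counts in an electronic diary under an independent assessor's direction, and "differences from baseline levels are compared at weeks 4 and 8".

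Section 4.4 says which drugs are meant: "The emergency treatment consisted of lactulose and glycerin enemas". Once its conditions are met (over three days without a stool, or intolerable symptoms), "they are allowed to use emergency medications under medical supervision with detailed documentation".

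The only express restriction on other gut-active drugs is inclusion criterion (5) in section 2.4.3.1: "No medications taken within 2 weeks prior to treatment that may affect gastrointestinal function, such as prucalopride and probiotics".

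The express drug rules that apply on study concern anti-Parkinson treatment. Section 2.4.3.3 rejects a case if "the dose or dosing regimen of the anti-Parkinsonian drug need to be adjusted during treatment", and section 4.1 adds: "Patients with any dosage adjustment, whether an increase, decrease, or adjustment, will be dropped".

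**The concern.** The name of the outcome makes two demands: the movement must be complete, and it must be spontaneous. The sentence that defines it leaves out the first and covers the second only in part.

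Completeness matters in this population. A feeling of incomplete evacuation is one of the Rome IV symptoms in section 2.4.2.2 and one of the six dimensions of the CSEAS, a secondary outcome. A patient could gain complete movements while the total stays the same, or gain only incomplete ones. The literal count cannot tell these apart, because it measures something nearer to spontaneous bowel movements.

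On drugs, the washout protects the baseline count, but no express rule gives the week 4 and week 8 counts the same protection. Section 2.2 names macrogol and lubiprostone as options for this constipation, and neither is an emergency drug. A stool after either would satisfy the written rule.

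At stake is whether the primary count means the same thing at baseline, week 4 and week 8, and whether it means what its name says. If completeness or drug use is not recorded when the movement happens, no later analysis can remove those movements.

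**Working it through.** The protocol gives no figure on this point, so the check compares the text section by section. The sample size is not in question. The pilot difference is 0.964 − (−0.321) = 1.285, and with SDs 1.726 and 1.310 an unequal-variance t-test needs 31 per group at two-sided 5% and 90% power. Then 31 / (1 − 0.20) = 38.75, rounded up to 39 per group, or 78 in total, as section 2.4.1.1 states.

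**Step 1: the name against the definition.**

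| Element of the name | What section 2.4.5.1.1 requires |
| --- | --- |
| Complete | Nothing |
| Spontaneous | No emergency medication |

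**Step 2: the scope of the drug condition.** Section 4.4 confines emergency treatment to lactulose and glycerin enemas. A movement after macrogol, lubiprostone, prucalopride or another laxative is not disqualified by the words used.

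**Step 3: whether another rule closes the gap.**

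| Section | Drugs covered | Period |
| --- | --- | --- |
| 2.4.3.1, criterion (5) | Drugs affecting gut function | 2 weeks before treatment |
| 2.4.3.3 | Anti-Parkinson drugs | During treatment |
| 4.1 | Anti-Parkinson drugs | Throughout the study |
| 4.4 | Lactulose, glycerin enemas (permitted on conditions) | On study |

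None expressly bars another laxative in weeks 1 to 8.

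**Step 4: what could be computed.** For each arm, let L be the mean number per patient per week of counted movements that follow a non-listed laxative. Let ΔI be the change from baseline in the mean number of other movements that are counted although incomplete. Taking L as about zero at baseline because of the washout, the literal rule shifts the MA − SA difference in change by

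shift = (L_MA − L_SA) + (ΔI_MA − ΔI_SA).

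The protocol gives no value for any of the four terms. The signs are also open:

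- More laxative use in the sham arm shrinks the difference, more in the manual arm inflates it, and equal L in both arms cancels.
- If acupuncture turned incomplete movements into complete ones with the total unchanged, ΔI_MA would be negative and the literal count would miss the benefit. If it added only incomplete movements, the literal count would show a benefit in complete movements that is not there.

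Any numerical result would come from invented inputs, so none is given.

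**The case against.** The strongest reply is that the intention is clear. Section 4.4 is a conditional permission: patients must first go over three days without a stool or have intolerable symptoms, use is supervised and documented, and the dose is fixed (two 15 ml lactulose doses 12 hours apart, or one enema). Rationing lactulose so tightly makes little sense if patients may take macrogol freely. They enter off gut-active drugs, and the outcome is called spontaneous. The diary, the case form and the consent text, where such instructions often sit, cannot be seen. Section 6 says patients are instructed beforehand and supervised throughout.

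Much of this stands. A reader might infer that the trial allows other laxatives on study; the documents do not support that, because section 4.4 implies the opposite. Nor do they show that the diary fails to ask about completeness. What remains is that section 2.4.5.1.1 supplies its own definition and that definition is wrong as written. Where the protocol wants an on-study drug rule it writes one, as it does for anti-Parkinson drugs.

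A reader might also infer that the primary result is biased towards acupuncture. Nothing shows that participants would use other laxatives, or use them unequally; section 2.2 is background only. Patient blinding makes an imbalance less likely up to week 4. Week 8 may have less of that protection, since "The blinding will be removed at the end of the treatment, and patients will be informed of their grouping after treatment". However, the same sentence also says that patients learn their type of acupuncture after follow-up, so what they know in between is unclear. Continued constipation in the sham arm would, if anything, prompt more laxative use there, which shrinks the difference.

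**Conclusion.** The point holds as a defect in a stated rule. It is certain that the definition omits completeness and names only emergency medication. It is also certain that, in the text available, the express bar on other gut-active drugs covers only the 2 weeks before treatment. Section 4.4 implies a wider bar but does not state it.

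The effect on the result is unknown in size and direction, and no bias is demonstrated. The conclusion is limited to the protocol text available and assumes that the written definition is the rule patients and assessors would follow. If the diary or patient instructions already ask about completeness and forbid other laxatives, the conduct may be sound and only the protocol sentence needs correcting. The correction is worth making because it concerns the primary outcome and costs almost nothing.

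**What to change.** 1. In section 2.4.5.1.1, define a CSBM as *a bowel movement with a feeling of complete evacuation and no laxative, enema, suppository, secretagogue or prokinetic (emergency or other) in the preceding 24 hours*. Apply it at baseline, week 4 and week 8 alike.
2. In section 4.4, add: *No laxative or other gut-active drug, including probiotics, beyond the emergency medications listed here is to be used through week 8. Any breach is recorded with its date in the electronic diary, and the patient stays in the intention-to-treat analysis.*
3. Handle probiotics through that bar and record only. They have no clear 24-hour effect, so disqualifying single movements after one would be arbitrary.
4. Make sure the existing diary asks, for each movement, whether it felt complete, and records other gut-active drugs by date. A new row in Table S1 is optional: that table is not exhaustive, since it also omits the vital signs required in section 3.

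The cost is one reworded sentence, two short additions and a small diary change, with slightly more burden on patients. Counts will be lower in patients who use other laxatives, and substantially lower in daily users. That is the intended meaning of *spontaneous*, but it is a choice and should be made knowingly. The protocol does not say how the pilot counted movements. If the pilot used the looser rule, its mean difference and SDs may not carry over exactly to the corrected outcome.

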2.4.1.1 Pilot study and Sample size

We conducted a pilot study to determine the sample size for the randomized controlled trial. Twenty-eight patients were chosen to receive either manual or sham acupuncture (14 patients in each group). We used the change in weekly complete spontaneous bowel movements (CSBMs) from baseline to the end of the trial as an evaluation. Patients who received MA had a mean CSBMs score of 0.964 (standard deviation [SD],1.726), whereas patients who received SA had a score of -0.321. (SD, 1.310). According to PASS version 15.0, 31 patients are needed for each group at a two-sided significance level of 5% and a power of 90%. The sample size estimation was shown in Supplementary Figure S1. With an estimated loss-to-follow-up rate of 20%, we will plan to enroll a total of 78 patients with 39 patients per group.

[figure not shown]

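### The primary outcome is compared at weeks 4 and 8 with neither week ranked and no success rule, while the trial is sized for one comparison at a week that is not clearly identified

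*Protocol*

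**What the plan says.** Three places in the protocol bear on this.

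- **Section 2.4.5.1.1 (primary outcome).** Weekly CSBMs are collected at weeks 0, 4 and 8, and "differences from baseline levels are compared at weeks 4 and 8". Both weeks stand under the primary outcome, and neither is put ahead of the other.
- **Section 5 (statistical analysis).** "Differences between groups were reported using 95% confidence intervals and bilateral P values, with values less than 0.05 considered significant". The section gives no testing order, no adjustment, and no statement of whether one week or both must succeed. It also mentions a repeated measures ANOVA, described as looking at trends and effects over time within groups.
- **Section 2.4.1.1 (sample size).** The pilot evaluated the "change in weekly complete spontaneous bowel movements (CSBMs) from baseline to the end of the trial". From that one change score the protocol derives 31 patients per group at two-sided 5% and 90% power, and 39 per group (78 in total) after allowing for 20% loss. The week that the phrase denotes is not given, nor is the length of the pilot.

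**The concern.** Benefit at the end of treatment (week 4) and benefit that persists four weeks later (week 8) are different claims. A reader of the protocol cannot tell which of them is the primary claim, or whether one or both must be shown. Two consequences follow.

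- Under the text as it stands, a primary success could be declared on whichever week reaches significance. A claim made that way does not have a 5% error rate.
- The 5% and 90% in Section 2.4.1.1 describe one test. It is unclear which of the two primary comparisons they belong to, and they do not describe the pair.

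**Working it through.** **Inputs.** From Section 2.4.1.1: mean change 0.964 (SD 1.726) with manual acupuncture and -0.321 (SD 1.310) with sham; two-sided 5%; power 90%; loss 20%. From Section 2.4.1.2: allocation 1:1. From Section 2.4.5.1.1: two time points. From Section 5: threshold 0.05. The correlation between the week 4 and week 8 test statistics is not given; I assume 0 to 0.9 and show the range.

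**1. The protocol's own figure.**

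- Difference: 0.964 + 0.321 = 1.285.
- Pooled SD: √[(1.726² + 1.310²)/2] = √2.348 = 1.532.
- Standard error at 31 per group: 1.532 × √(2/31) = 0.389. Noncentrality: 1.285/0.389 = 3.30 on 60 degrees of freedom.
- Two-sided t-test power at 0.05: 90.1% at 31 per group, 89.1% at 30. So 31 is reproduced.
- Loss: 31/0.8 = 38.75, rounded up to 39 per group, 78 in total. Also reproduced.

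The sample size is correct as a calculation for one test. It contains no allowance for a second.

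**2. If success at either week counts.** The false-positive rate is 1 − P(|Z₁| < 1.96 and |Z₂| < 1.96), with Z₁ and Z₂ standard normal with correlation ρ. For ρ = 0 this is 1 − 0.95² = 9.75%.

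| ρ (assumed) | 0 | 0.5 | 0.7 | 0.8 | 0.9 |
|---|---|---|---|---|---|
| False-positive rate | 9.75% | 9.1% | 8.3% | 7.8% | 7.0% |

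It stays above 5% for any ρ below 1.

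**3. If both weeks must be significant.** The chance of a false joint claim cannot exceed 5%. Joint power is P(Z₁ > −z and Z₂ > −z), where z is the normal quantile of the power of each single test. I assume the same effect and SD at both weeks.

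| ρ (assumed) | 0.5 | 0.7 | 0.8 | 0.9 |
|---|---|---|---|---|
| 31 evaluable per group (90% per test) | 83% | 85% | 86% | 87% |
| 39 evaluable per group (95.5% per test) | 92% | 93% | 93% | 94% |

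**4. If alpha is split at 0.025 per week.** Power per test is 83.9% at 31 evaluable per group and 91.9% at 39. To have 90% after the planned loss would take 37 evaluable per group; 37/0.8 = 46.25, so 47 per group and 94 in total.

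**5. Which week was sized?** Section 2.4.5.3 uses the same phrase, the end of the trial, for the moment when patients guess their allocation. Table S1 marks the blinding assessment at weeks 0 and 8 and not at week 4. Section 2.4.5.1.1 labels week 4 as post-treatment. By the protocol's own usage the sized week is therefore probably week 8. This is not conclusive, because Section 2.4.1.1 describes the pilot, whose duration is not stated.

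**The case against.** A reader might infer that the trial's false-positive rate simply is above 5%. The documents do not support that. No section says that success at either week is enough; the inflation in step 2 belongs to that one rule, which the text allows but does not adopt. Nor does the protocol state an error rate across both weeks: the 5% in Section 2.4.1.1 is the level of the sizing test.

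A reader might also infer that 90% power is not delivered. That holds for the joint requirement or a split alpha at 31 evaluable per group, which is the full planned loss. If all 39 are evaluable, both exceed 90%. Section 5 plans intention-to-treat with imputation, so the practical position lies somewhere between the two.

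A third tempting step is to make week 4 primary because treatment ends then. The documents give no ground for preferring it, and their wording leans to week 8 as the week that was sized. If the pilot figures are week 8 changes, no effect or SD has been given for week 4.

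Finally, a statistical analysis plan that is not shown may set a testing order. That is fair, and the lack of multiplicity detail alone would not be a finding. What remains is what the protocol does fix: two unranked primary comparisons, one threshold for each, and a sample size for one comparison at an unclear week. The repeated measures ANOVA does not close the gap, since it is described as a within-group analysis and is not named as an overall between-group test that must succeed first.

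**Conclusion.** The point holds in conditional form. The protocol sets two primary comparisons of equal standing and sizes one, without fixing the primary week or the rule for success. Under an either-week rule the false-positive rate is 7.0% to 9.75% (correlation 0.9 to 0). Under a both-weeks rule the error rate is controlled, and joint power is about 83% to 87% at 31 evaluable per group or above 90% if all 39 are evaluable (correlation 0.5 to 0.9). These ranges rest on assumed correlations, and the joint power also on an effect that is the same four weeks after treatment stops. The sample size arithmetic itself is right. The defect is easily mended, but it decides what the trial may claim as its primary result.

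**What to change.** - In Section 2.4.5.1.1, name one primary time point, the same one to which the pilot difference in Section 2.4.1.1 refers, tested at two-sided 0.05.
- Make the other week the first secondary test, confirmatory only if the primary test is significant.
- In Section 2.4.1.1, state which week the pilot means and SDs describe.
- If the sponsor prefers the other week as primary, restate the power for that week from an effect and SD that belong to it; the sample size might then change.

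If the primary week is the sized week, this is a change of wording only: alpha stays at 5% and the numbers stay at 31, 39 and 78. The price is that the non-primary week can no longer carry the trial alone.
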